## 3. Materials and Equipment

Potential material donors for FMT are:

Healthy pregnant women from a group of at least 20, who consented to the collection of material from them, were positively screened around 20 weeks of pregnancy. The screening process included a detailed health questionnaire.

FMT material will be collected around 32 weeks of pregnancy from previously selected individuals and positively qualified in accordance with the donor qualification protocol, as recommended internationally and outlined in the proprietary method developed by Human Biome S.A. [29].

The conditions for the release of gut microbiota products are:-A negative smear test for Streptococcus agalactiae (group B streptococcus, GBS) before the start of material donation (around the 20th week of pregnancy) and at 35–37 weeks of pregnancy (routine testing of pregnant women for GBS).-Full-term delivery (full-term pregnancy), i.e., between 37 + 0 and 41 + 6 weeks of pregnancy.-No perinatal complications—confirmed on the basis of a telephone interview with the donor.-No reported health problems after delivery in the mother and child—confirmed on the basis of a telephone interview with the donor.

Due to the proven effectiveness of transplants from unrelated donors [30], the donor of choice in the experiment will be an unrelated donor who meets all the criteria necessary to ensure the biological safety of the material administered to recipients.

The material will be supplied in 8-millilitre syringes. No additional medical equipment is required.

## 4. Detailed Procedure

### 4.1. Transplant Recipients Procedures

FMT will be administered to patients in the study group who meet the inclusion criteria and do not meet the exclusion criteria, in the form of a deep rectal infusion, in a volume of 5 mL, twice at 6 h intervals, between 3 and 6 days after birth and/or up to 14 days in patients who experience temporary contraindications to the use of FMT or in patients who will be transferred to our center for treatment from an external facility.

In the first phase of the experiment, 10 patients from the study group born between 28 0/7 and 36 6/7 will undergo the procedure. All adverse effects of the therapy will be monitored and documented on an ongoing basis. If no serious adverse events (SAEs) occur, we will include another 10 patients born between 24 0/7 and 27 6/7 in the study (phase two of the experiment).

A serious adverse event (SAE) is defined as any medical event that, at any dose, meets at least one of the following criteria:Leads to death.Is life-threatening to the participant.Requires hospitalization or prolongs hospitalization.Leads to permanent or significant impairment of function or disability.A detailed description of the monitored parameters is provided below.

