### 2.2. Trial Design

This will be a safety study of FMT for the prevention of NEC, in the form of a prospective, open-label study with continuous recruitment of up to 40 patients in total (20 in the study group, 20 in the control group). Included patients must meet the exact inclusion criteria described below and must not meet any exclusion criteria. The study group will include 10 premature infants born between 28 0/7 and 36 6/7 weeks of gestation, followed by another 10 premature infants born between 24 0/7 and 27 6/7 weeks of gestation, and 20 premature infants in the control group. After completion of this stage (inclusion and treatment of 20 patients + 20 in the control group), the safety of the therapy will be assessed with a description and presentation of all adverse events, their classification and relationship to the intervention.

The safety of the therapy will be assessed by comparison with a control group, i.e., 20 patients who will meet the same inclusion criteria and will not meet any of the exclusion criteria, subject to the same hospital observation but without undergoing any medical/therapeutic intervention other than the collection of biological material (including stool, blood and urine samples for exploratory testing of the gut microbiota).

Recruitment will occur continuously between January 2026 and January 2027. The study is registered at ClinicalTrials.gov (NCT06333405).

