#### 2.3.1. Sample Size

A formal sample size calculation based on power analysis was not performed, as this is a pilot safety study intended to generate preliminary data (estimates of adverse event rates) for a future randomized controlled trial (RCT). A sample size of 20 subjects in the intervention group was determined based on feasibility constraints and standard recommendations for pilot safety studies, following biostatistical consultation [28]. In the first phase, 10 patients born between 28 0/7 and 36 6/7 will be included, followed by 10 patients born between 24 0/7 and 27 6/7 in the second phase.

The control group will include 20 matched controls—patients who meet the same inclusion and exclusion criteria as the study patients.

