#### 2.3.2. Allocation

During the safety study phase, we plan to enroll the first 20 patients who meet the inclusion criteria and do not meet the exclusion criteria, who will be admitted to the clinic during the study.

The list will be available to all department physicians who will be involved in the study and trained in study procedures. These will also be the individuals who will decide on the administration of FMT to patients and observe them after the procedure.

Patients will be included in the control and study groups in a 1:1 ratio according to the order of admission to the ward. This means that each subsequent patient included in the study will be included in the opposite group to the previous patient.

The study will not be blinded.

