#### 2.3.3. Statistical Analysis

All analyses will be conducted on an intention-to-treat basis.

The primary endpoint is safety, defined as the incidence of adverse events (AEs) and serious adverse events (SAEs) during the observation period.

The proportion of patients experiencing at least one AE or SAE will be compared between groups using Fisher’s exact test. The chi-square test will be applied when its assumptions are met.

The incidence of specific AEs will also be compared using Fisher’s exact test. Relative risks (RRs) with two-sided 95% confidence intervals (CIs) will be calculated.

If the number of events per patient is analyzed, between-group comparisons will be performed using Poisson regression or negative binomial regression, depending on data dispersion.

Time to first AE, if applicable, will be analyzed using Kaplan–Meier estimates and compared using the log-rank test.

Continuous variables will be assessed for normality using the ShapiroWilk test. Normally distributed variables will be compared using Student’s *t*-test, and non-normally distributed variables using the Mann–Whitney U test.

Two-sided tests will be used throughout, with statistical significance set at α = 0.05. Estimates will be presented with two-sided 95% confidence intervals. Analyses will be performed using validated statistical software (e.g., R, Stata, or SAS); the exact software and version will be documented in the final report.

Given the limited sample size, the study is not powered for formal hypothesis testing of small effect sizes. Therefore, interpretation will focus primarily on effect size estimates and their 95% confidence intervals rather than solely on statistical significance. Clinically meaningful differences will be considered in the context of effect magnitude and precision.

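### A zero-SAE condition applied only to the first 10 FMT infants, followed by a pooled 20 versus 20 comparison, makes the completed-trial SAE rate and relative risk lean towards FMT

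*Protocol article*

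**What the plan says.** Section 4.1 (Transplant Recipients Procedures) sets the first step: "In the first phase of the experiment, 10 patients from the study group born between 28 0/7 and 36 6/7 will undergo the procedure". Continuation follows: "If no serious adverse events (SAEs) occur, we will include another 10 patients born between 24 0/7 and 27 6/7 in the study". The condition refers to the study group. No observation window and no requirement of relatedness is attached to it. The SAE definition below it covers any medical event that meets a seriousness criterion.

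Section 2.2 (Trial Design) times the assessment: "After completion of this stage (inclusion and treatment of 20 patients + 20 in the control group), the safety of the therapy will be assessed".

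Section 2.3.1 (Sample Size) says "The control group will include 20 matched controls", with the same eligibility criteria as the study patients. Section 2.3.2 (Allocation) states "Patients will be included in the control and study groups in a 1:1 ratio according to the order of admission to the ward". Neither these sections nor section 4.4 places an SAE condition on controls.

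Section 2.3.3 (Statistical Analysis) gives one between-group comparison: "The proportion of patients experiencing at least one AE or SAE will be compared between groups using" Fisher's exact test, or chi-square where its assumptions are met. It adds: "Relative risks (RRs) with two-sided 95% confidence intervals (CIs) will be calculated". The level is 0.05 two-sided. Nothing separates the phases or refers to the continuation condition. The same section says that interpretation will rest mainly on effect estimates and their intervals.

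**The concern.** SAEs are part of the primary endpoint. The decision to continue looks at that component in one arm and lets the trial proceed only when the count is zero. A trial that reaches 20 + 20 therefore has half of its FMT arm selected for a good SAE result, while the controls keep their background rate. Pooling the phases carries this selection into the FMT proportion, the relative risk and its interval.

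The direction matters because it favours the hypothesis in section 2.1, an adverse event profile comparable to standard care. A pooled SAE relative risk at or below 1 could arise from the selection alone, and a real increase in SAEs could be understated. Section 5.4 gives the detection of safety signals for later randomized trials as the main aim. Its limitations cover the open label, non-random allocation and small size, but not this selection.

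**Working it through.** The protocol gives no SAE rate, power or operating characteristic for the condition, so there is no stated figure to reproduce.

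**Inputs from the protocol.** 10 FMT infants at 28–36 weeks must have no SAE before 10 more at 24–27 weeks are added (4.1). There are 20 controls without that condition (2.3.1, 2.3.2). The comparison is pooled at two-sided 0.05 (2.2, 2.3.3).

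**Assumptions.** p1 and p2 are the SAE risks per infant in phase-one-type and phase-two-type infants. They are equal in both arms under no effect. Controls have the same 10 + 10 mix. An SAE of any cause closes the gate to phase two. g is the share of phase-one SAEs already known when the decision is made.

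**Step 1: chance of continuing.** With g = 1 this is (1 − p1)^10, which gives 60%, 35%, 11% and 2.8% for p1 = 5%, 10%, 20% and 30%.

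**Step 2: expected rates given continuation.** A phase-one FMT infant with no SAE known at the decision has a later SAE with probability r = (1 − g)p1 / (1 − g·p1). The expected FMT rate is (r + p2)/2 and the control rate is (p1 + p2)/2. The ratio of expected rates, truly 1, is (r + p2)/(p1 + p2). With g = 1 it reduces to p2/(p1 + p2).

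| p1 / p2 | all known (g = 1) | half known | a quarter known |
|---|---|---|---|
| 20% / 20% | 0.50 | 0.78 | 0.89 |
| 10% / 20% | 0.67 | 0.84 | 0.92 |
| 5% / 20% | 0.80 | 0.90 | 0.95 |

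Example, 10%/20% with half known: r = 0.05/0.95 = 0.0526, and (0.0526 + 0.20)/0.30 = 0.84.

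**Step 3: true harm.** With control risks of 10%/20% and a true relative risk of 2, FMT risks are 20%/40%. With g = 1 the ratio is 0.40/0.30 = 1.33. With half known, r = 0.10/0.90 = 0.111 and the ratio is 0.511/0.30 = 1.70.

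**Step 4: false significance.** All 21 × 21 tables were enumerated, using Fisher's test and switching to chi-square when expected counts reach 5. Given continuation and g = 1, the chance of p < 0.05 with no true effect is 1.6% at 10%/10%, 7.5% at 20%/20%, 8.3% at 20%/40% and 16% at 30%/30%, nearly all of it favouring FMT. At 20%/20% it falls to 3.8% with half known and 3.3% with a quarter known. At 30%/30% with half known it is 6.7%.

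**Step 5: the bias is conditional on completion.** With equal risks p and g = 1, averaging the FMT rate over stopped and completed trials gives p + (1 − p)^10 × p/2. At p = 10% this is 0.10 + 0.349 × 0.05 = 0.117, slightly against FMT. The lean towards FMT belongs to the 20 + 20 analysis.

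**The case against.** A reader might infer that every completed trial must show 0/10 SAEs in phase one. The documents do not support that. The abstract counts SAEs until hospital discharge, section 5.3 expects stays of several weeks, and section 4.1 gives the condition no window. Section 4.3 counts SAEs over 72 hours after FMT, but nothing ties the condition to that period. An infant can pass the decision and have an SAE later. At 20%/20% with half of the SAEs known, phase one ends at 0/10 with probability (1 − 0.111)^10, about 31%. This shrinks the bias, as the table shows. It does not remove it while any phase-one SAE could have closed the gate.

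Relatedness is a second limit. The sentence before the condition speaks of adverse effects of the therapy, and section 2.2 plans to classify each event's relationship to the intervention. If only related SAEs count, background events do not select the arm and the no-effect bias largely disappears. The SAE definition favours the all-cause reading, but the text is not decisive.

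Third, the combined AE-or-SAE proportion moves less. Assuming independent non-serious AE risks of 60%/80% with SAE risks of 10%/20%, control proportions are 1 − 0.4 × 0.9 = 0.64 and 1 − 0.2 × 0.8 = 0.84. The FMT values given g = 1 are 0.60 and 0.84, so the ratio is 1.44/1.48 = 0.97.

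Fourth, a reader might infer from section 2.2 that a trial stopped after phase one goes unreported. That section schedules the assessment after 20 + 20. It does not say that only completed trials are reported, and section 4.1 has adverse effects documented as they occur. What is left is that the stopped case is not addressed.

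Finally, sections 2.3.3 and 5.4 already urge caution and put estimates before significance. That helps with type I error but not here, because the estimates are what is distorted.

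**Conclusion.** The concern stands for the SAE rate and SAE relative risk in a trial that reaches 20 + 20: both lean towards FMT because one arm is selected on the outcome and the phases are then pooled. The size cannot be fixed from the protocol. Under no true effect and all-cause gating, the assumed scenarios in the table give ratios from 0.50 to 0.95. The ratio is closer to 1 when phase-one SAEs are rare, when many occur after the decision, or when only related SAEs count.

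A broader claim, that the plan's significance tests are generally invalid, is not supported. Type I error clearly exceeds 5% only at phase-one SAE risks of about 20% or more, and at 20%/20% only if nearly all SAEs are known at the decision. With all SAEs known, such trials continue in 11% of cases or fewer. The main damage is to estimates and intervals. Reading the continuation condition as a strict only-if is natural, but the protocol does not spell out what follows an SAE. The finding is worth correcting before analysis and does not require a change of design.

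**What to change.** In section 2.3.3:

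- Report SAEs separately for phase one and phase two, each against controls of the same gestational band.
- Present the phase-two comparison as the one free of the continuation condition.
- Show phase-one FMT SAEs with an exact two-sided 95% interval and a note that no SAE was the condition for continuing. If the count is 0/10, the upper limit is 1 − 0.025^(1/10) = 31%.
- Label any pooled SAE relative risk as conditional on that decision.

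In section 2.2, state that the AE/SAE comparison is also reported on all included infants, with their controls, if enrolment ends after phase one.

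The cost is a few sentences and no new data. The phase-two comparison rests on about 10 versus 10 infants at 24–27 weeks, so its interval is wide and it says nothing about 28–36 weeks. For that reason it should stand beside the phase-one and labelled pooled results, not replace them. It also needs controls identifiable by gestational band, and sections 2.2 and 2.3.1 do not split the 20 controls. The continuation rule itself stays as it is.

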### 4.2. Protocol for Administering Fecal Microbiota Preparation

Check whether the patient is eligible for FMT therapy according to the inclusion criteria.Assessing possible contraindications to FMT therapy (according to the exclusion criteria).Discuss the therapy with the patient’s parents/guardians and obtain their consent for the child to participate in the experiment. Also obtain consent for the processing of personal data and the use of biological material samples for scientific purposes, as well as for participation in surveys and follow-up on the therapy’s effectiveness.Collection of blood inflammation parameters (leukocyte count, CRP and procalcitonin) at the “point 0” stage, i.e., before the administration of microbiota.Ensure that biological material samples are collected before (point “0”) FMT (feces, urine and blood samples), as described in the section below. Alternatively, collect samples before administering FMT.Familiarize yourself with the characteristics of producing donor intestinal microbiota preparations in the form of a suspension (MBiotix^®^ HBI; Warsaw, Poland) and with the procedure for administering the therapy to patients.Verify the presence of temporary contraindications to FMT administration.Obtain the FMT preparations from the storage location.Thaw the suspension in accordance with the characteristics of the FMT suspension production service and/or the manufacturer’s instructions. The suspension does not require special thawing conditions; allow the syringe to thaw in an uncovered container at an ambient temperature of 22–25 °C for approximately 2–2.5 h.Administer two doses of intestinal microbiota (FMT1 and FMT2).

Due to the high safety profile of this form of FMT administration, patients will receive the preparation via deep rectal infusion using a soft Foley catheter.

The catheter will be connected to a syringe containing the suspension, and its lumen will be filled with the suspension to minimize the risk of oxygen entering the intestinal lumen.

The Foley catheter will then be inserted into the rectum to a depth of approximately 10–15 cm. After placement, 5 mL of the preparation (from a syringe containing 8 mL of the suspension) will be slowly administered directly into the catheter. Ultrasound guidance will be used to confirm the correct position of the Foley catheter and ensure the preparation is administered to the correct location—the cecum area.

After 5 mL of suspension has been administered, up to 2 mL of saline solution should be administered into the catheter for rinsing (depending on the size of the catheter). A certain volume of the product (approximately 3 mL) will remain in the syringe containing the suspension.

This procedure will be performed twice, at 6 h intervals (FMT1 and FMT2).

After each dose (FMT1 and FMT2), the catheter should be kept in the rectum for up to five minutes, and the patient should be placed in the Trendelenburg position and turned from side to side to ensure the preparation is distributed evenly throughout the intestine.

### 4.3. Monitoring the Transplant Recipients After the Procedure

Based on experience with FMT, the highest risk of developing sepsis, a rare but dangerous complication, occurs within the first six hours after the preparation is administered. Therefore, after the procedure, the patient will be continuously monitored.

The following will be assessed for the next 72 h after FMT administration:The number of episodes of oral feeding intolerance, diarrhea and the presence of blood, mucus or pus in the stool.The appearance of symptoms of infection or significant changes in vital signs (ECG, heart function and saturation—continuous measurement; blood pressure—4 times a day; temperature).The number of cases of NEC developed.Observation of other symptoms, such as convulsions, inconsolable crying and anxiety.The number of positive blood cultures and the percentage of antibiotic therapy use.Number of serious adverse events (SAEs), e.g., death, serious threat to health and/or life, and/or deterioration of health.

Blood inflammation parameters (leukocyte count, CRP and procalcitonin) will be collected before administration of the preparation (FMT1) and no later than 6–12 h after administration of FMT2, then every 12–24 h up to 72 h after FMT, depending on the patient’s condition.

A blood culture will be taken in the event of a significant increase in inflammatory parameters.

If any of the above-described criteria for temporary postponement of microbiota administration occur between FMT1 and FMT2 but resolve within 6 h (reassessment of the child’s condition after a minimum of 6 h) and do not recur within the next 6 h, the second dose of microbiota (FMT2) may be administered.

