## Abstract

**Background/Objectives**: Necrotizing enterocolitis (NEC) is an inflammatory disease with an incidence of about one in 1000 live births, much higher in premature and low birth weight newborns. Intestinal dysbiosis is an important element in the pathogenesis of NEC, and for this reason, experimental models have been used to administer fecal microbiota transplants (FMTs) for prophylaxis and treatment of NEC with very satisfactory results. The primary endpoint of the study is safety, defined as the incidence of adverse events (AEs) and serious adverse events (SAEs) occurring from the time of intervention until hospital discharge, classified according to severity and assessed for relatedness to the intervention. **Methods**: This prospective, single-arm, open-label clinical study will include 20 infants born between 24 0/7 and 36 6/7 weeks of gestation. FMTs will be administered twice as a deep rectal infusion via a Foley catheter. The donors of the material from which the FMT will be prepared will be women in the third trimester of pregnancy. The safety of the therapy will be assessed by comparison with a control group, i.e., 20 patients who will meet the same inclusion criteria and will not meet any of the exclusion criteria, subject to the same hospital observation but without undergoing any medical/therapeutic intervention other than the collection of biological material. **Discussion**: The study will provide data on the safety and initial efficacy of FMT in this group of patients, which will allow for further research into the use of this method in the prevention of infections and NEC. Ethics: The study protocol was approved by the Bioethics Committee of the Medical University of Warsaw, Warsaw, Poland (KB/52/2025). All procedures will follow the principles of the Declaration of Helsinki. The results of the study will be submitted for knowledge translation in peer-reviewed journals and presented at national and international pediatric society conferences. Clinical Trial Registration: The study is registered at ClinicalTrials.gov: ID: NCT06333405.

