## 1. Introduction

Necrotizing enterocolitis (NEC) is an inflammatory disease affecting one in 1000 live-born newborns. Due to NEC, 2–5% of newborns are hospitalized annually in neonatal intensive care and pathology units. Overall, 85% of all cases of NEC occur in neonates born <32 weeks of gestation (WG) and/or weighing <1500 g. The risk increases with decreasing gestational age. At 22–28 WG, it is 11%; at 28–32 WG, it is 9% and increases to 13% with coexisting congenital heart disease [1,2]. The mortality rate in the general population of patients with NEC is between 15 and 30%, depending on the study, and has remained unchanged for many years [3,4]. The current treatment regimen for NEC is based on symptomatic interventions—cessation of enteral feeding, antibiotic therapy, and, in complicated cases, surgical intervention [1].

According to the most recent studies, intestinal dysbiosis, i.e., altered patterns of intestinal colonization, resulting in abnormal intestinal microbiome composition and microbiota function, plays a very important role in the pathogenesis of NEC and other infectious complications, like neonatal sepsis [5,6,7]. Dysbiosis initiates an unbalanced pro-inflammatory response of the immune system in premature infants, which ultimately leads to a breakdown of the intestinal mucosal barrier, intestinal bacterial translocation, and intestinal necrosis [6,8]. In the study by el Manouni el Hassani et al., it was shown that in both Gram-negative and Gram-positive late-onset sepsis LOS combined, the causative pathogen could be identified in at least one fecal sample collected 3 days prior to LOS onset in the majority of the fecal samples, whereas these pathogens were present in about one-third of control samples [9].

Antibiotic therapy in the mother and newborn, method of delivery, birth weight and birth age have been proven to affect the microbiome [6,10]. Vaginal delivery and breastfeeding ensure the formation of the correct microbiota and microbiome pattern of the gastrointestinal tract in the newborn. Breastfeeding is one of the main preventive factors for NEC, but it is often challenging to achieve for premature newborns due to both neonatal and maternal factors. On the other hand, formula feeding predisposes to the development of NEC through significant changes in the intestinal microbiota [11].

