### 4.4. Procedures for the Patients in the Control Group

Check whether the patient meets the inclusion criteria for the experiment.Check whether the patient meets the exclusion criteria.Discuss the purpose and procedures of the experiment with the patient’s parents/guardians and obtain their informed consent for the child’s participation in the experiment. This includes consent for the processing of personal data and the use of biological material samples for scientific purposes, as well as consent for participation in surveys and follow-up on the effectiveness of therapy.Collect blood parameters indicating inflammation (leukocytosis, CRP, procalcitonin) at the “0” point (“BEFORE intervention”), between signing the consent form and the fifth day of the child’s life.Ensure that biological material samples (feces, urine and blood samples) are collected before (point “0”) FMT, as described in the section below, or collect samples before the sixth day of the child’s life.For the control group, the matching time point for administering gut microbiota doses and counting “post” days is assumed to be the sixth day of the child’s life.From day 6 (the matching time point), any adverse events or deviations from the norm will be recorded, such as deterioration in general condition, appearance of symptoms of infection or increase in inflammation indicators.Blood inflammation parameters (leukocytosis, C-reactive protein (CRP), procalcitonin) will be collected during the “post-matching time point” period at least once within 72 h of day 6, or more frequently if the patient’s clinical condition requires it, as assessed by the attending physician.

The following will also be recorded in both study groups:-The number of days spent in hospital;-Percentage increase in body weight (birth weight vs. weight at discharge);-The number of days of antibiotic therapy received during hospitalization (monitoring until discharge from the hospital conducting the experiment).

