### 5.2. Secondary Outcomes

The following parameters will also be analyzed:-Duration of hospitalization.-Weight gain (percentage increase from birth to discharge).-Length of antibiotic therapy.-Incidence of other infectious or inflammatory complications.

The collected biological material will also enable the exploratory analysis of microbiota composition and its changes throughout the experiment.

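### The event window for the primary safety endpoint differs between sections and between arms, and the abstract promises early efficacy data although NEC is not a named outcome

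*Protocol article*

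**What the plan says.** Four places in the protocol article bear on when events are counted.

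- The abstract defines the primary endpoint as AEs and SAEs from the intervention until the infant leaves hospital.
- Section 2.3.3 (Statistical Analysis) ties the same endpoint to an observation period that is not defined.
- Section 4.3, on treated infants only, states "The following will be assessed for the next 72 h after FMT administration". Its list contains "The number of cases of NEC developed", then "The number of positive blood cultures and the percentage of antibiotic therapy use", and then "Number of serious adverse events (SAEs), e.g., death, serious threat to health and/or life, and/or deterioration of health".
- Section 4.4, on controls, states "From day 6 (the matching time point), any adverse events or deviations from the norm will be recorded". It gives no end date, and its examples do not mention NEC or cultures.

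On outcomes, section 5.1 names safety through adverse event reporting. Section 5.2 lists length of stay, weight gain, length of antibiotic therapy and "Incidence of other infectious or inflammatory complications". Neither names NEC. The abstract nevertheless says "The study will provide data on the safety and initial efficacy of FMT in this group of patients".

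The Introduction gives the NEC risk by gestational age: "At 22–28 WG, it is 11%; at 28–32 WG, it is 9" per cent. The same sentence raises this to 13% with congenital heart disease.

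**The concern.** The primary analysis in 2.3.3 compares the proportion of infants with at least one AE or SAE between groups. That comparison is fair only if the same events are looked for over the same period in both groups. As written, the two procedural sections give different lists and different periods. The discharge end point for adverse events appears only in the abstract, whereas ward staff will work from 4.3 and 4.4.

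A site that took 4.3 literally could close the structured count of NEC, positive cultures and SAEs for a treated infant at 72 h, while still recording NEC in a control in week 4. The loss would fall on one group only and would make FMT look safer and more protective than it is. Section 4.1 also makes the second phase depend on no SAE having occurred, without stating a period, so it inherits the same ambiguity.

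Separately, section 2.2 describes a safety study of FMT for preventing NEC. A promise of early efficacy data needs a named NEC outcome and enough cases to say something, and neither is in place.

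**Working it through.** The protocol gives no power, effect size or expected event count. Section 2.3.1 bases the 20 infants in the intervention group on feasibility, so there is no derived figure to reproduce.

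**Step 1. The passages side by side**

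| Place | Group | Start | End | Events |
|---|---|---|---|---|
| Abstract | both, by comparison | intervention | discharge | AEs, SAEs |
| 2.3.3 | both | not defined | not defined | AEs, SAEs |
| 4.3 | FMT | FMT | 72 h | includes NEC, positive cultures, antibiotic use, SAEs |
| 4.4 | control | day 6 of life | none given | any adverse event |

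**Step 2. Consequence of each reading**

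Let f be the share of NEC in treated infants that begins within 72 h, and RR the true risk ratio.

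- 4.3 taken literally, controls followed to discharge: apparent RR = f × RR. This is below the true value whenever f is less than 1, so the error favours FMT.
- Abstract window in both groups: apparent RR = RR, with no bias from this source.

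The document gives no distribution of NEC onset, so f cannot be filled in.

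**Step 3. Expected NEC cases with one window to discharge**

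Inputs: 11% (22–28 weeks) and 9% (28–32 weeks) from the Introduction; 10 infants in each gestational stratum from section 2.2. That split is stated for the study group only and is assumed here for controls.

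- Expected cases per group: 10 × 0.11 + 10 × 0.09 = 1.1 + 0.9 = 2.0.
- Probability of no case in a group: 0.89^10 × 0.91^10 = 0.312 × 0.389 = 0.12.
- Other control splits: 20 × 0.09 = 1.8 (all older) to 20 × 0.11 = 2.2 (all younger).
- If every infant in the older stratum had heart disease: 1.1 + 10 × 0.13 = 2.4.
- In the other direction, the 9% is given for 28–32 weeks but is applied here up to 36 6/7 weeks. The Introduction says risk falls as gestational age rises, so 2.0 leans high in that respect.

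**Step 4. What 20 per group can show**

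Two-sided Fisher's exact test, as in 2.3.3, with no cases in one group of 20:

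| Cases | p |
|---|---|
| 2 vs 0 | 0.487 |
| 4 vs 0 | 0.106 |
| 5 vs 0 | 0.047 |

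The average risk is 2.0/20 = 10%. Exact power at α = 0.05 is then 4.3% if FMT removed all NEC (10% vs 0%) and 1.7% if it halved it (10% vs 5%). With the 15% attrition anticipated in section 5.3 (20 × 0.85 = 17 per group), these become 2.2% and 1.0%. Detecting a halving from 10% with 80% power would need about 435 infants per group. The halving and the elimination are illustrative assumptions.

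**The case against.** The strongest reply is that the endpoint window is stated and that 4.3 is not meant to replace it. The abstract runs to discharge. Section 2.2 promises controls the same hospital observation, and section 4.1 says adverse effects are documented on an ongoing basis. Section 4.3 opens with the early sepsis risk and sets out continuous vital signs and repeated laboratory tests, which reads as post-procedure monitoring. Nothing in it says that recording stops at 72 h. Antibiotic use is in the 72 h list, yet 4.4 records antibiotic days in both groups until discharge, so the list is not exclusive. All of this stands. A reader might infer that late NEC after FMT will be undercounted; the documents support only that it could be, on one literal reading.

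The direction of error is also not one-sided. After FMT, inflammatory markers are taken every 12–24 h up to 72 h; controls need them at least once within 72 h of day 6. Denser sampling tends to raise early detection in the FMT group. It does not recover late events, but it is a further difference in observation between the groups.

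On NEC as an outcome, the document calls NEC an inflammatory disease, so the generic item in 5.2 can include it, and section 5.4 says Bell's criteria are applied. On efficacy, sections 2.3.3 and 5.4 admit low power and leave efficacy to later randomized trials. These points soften the concern. They do not define the observation period in 2.3.3, give 4.4 an end, or bring the abstract's wording into line with the body of the text.

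**Conclusion.** The concern holds as an inconsistency. The primary endpoint has a window to discharge, an undefined window, a 72 h list for one group and an open-ended record for the other. Whether this biases the comparison depends on which text is followed: the bias is zero under the abstract's window and favours FMT under a literal 4.3. The documents do not allow its size to be estimated, because they give no onset times for NEC.

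The efficacy promise should be withdrawn for a different reason. A reader might infer that the 72 h list itself prevents the design from giving efficacy data. That does not follow, because the abstract's window would capture later NEC in both groups. The limit is size: about 2 expected cases per group, against the 5 versus 0 that Fisher's test requires. The figure of 2 assumes a 10/10 gestational split in both groups and no heart disease, and it is not a strict ceiling. Over the alternatives in the check it runs from 1.8 to 2.4, which leaves the conclusion unchanged.

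**What to change.** - In 2.3.3, 4.3 and 4.4, state that the same listed events (NEC by Bell's criteria, culture-positive sepsis, death, all AEs and SAEs) are counted in both groups from time zero to hospital discharge. Define time zero once for each group.
- In 4.3, state that the 72 h is a period of intensive monitoring and not the endpoint window.
- In 5.2, name NEC and late-onset sepsis as descriptive secondary outcomes.
- In the abstract, replace the promise of initial efficacy with descriptive NEC and sepsis counts, and say that no efficacy conclusion will be drawn.

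The cost is wording. Section 5.3 expects stays of several weeks, so the infants are already under observation and no procedure or visit is added. The one downside is that the stated ambition becomes slightly less favourable.
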